### 2.3. Sample Size

The sample size was calculated using an a priori power analysis conducted with G*Power software (version 3.1.9.7). The calculaion was based on a mixed-design repeated-measures ANOVA with one between-subjects factor (three groups) and one within-subjects factor (three time points). A conservative medium effect size (f = 0.32) was selected for the calculation, which represents a smaller effect than that reported by Aphiphaksakul et al. [31], who reported functional improvements following a mobili-application-based training protocol in stroke patients. This effect size corresponds to an expected between-group difference of approximately 8–10 points on the Barthel Index, substantially exceeding the established MCID of 1.85 [32,33], thereby ensuring clinically meaningful differences. The analysis employed a significance level of α = 0.05 and a statistical power of 0.80 (1 − β = 0.80), and 10% dropout rate. Based on these parameters, the required sample size was determined to be 75 participants, with 25 participants allocated to each group.

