Given the number of secondary outcomes, results will be interpreted cautiously, and multiplicity will be addressed using appropriate statistical adjustments, as detailed in Section 2.8.

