### 2.8. Statistical Analysis

The statistical analysis will be performed with the IBM SPSS v.26.0 software. Descriptive statistics will be calculated for all variables. To check the normal distribution of the variables, the Kolmogorov–Smirnov test with the Lilliefors correction will be used. For the comparison of the groups, a mixed 3 × 3 ANOVA will be carried out with interaction time (three measurement time points) and group (three intervention groups). The assumption of sphericity will be checked by means of the Mauchly test; if it is not met, the Greenhouse–Geisser correction will be used for interpretation.

The primary outcome and the Key Secondary Outcomes (motor function, muscle tone, muscle strength, balance, and quality of life) will be analyzed following this main model, given their clinical relevance. Additional Secondary Outcomes (gait performance, perceived pain, fatigue, fall risk, and subjective perceived change) will be analyzed using the same statistical approach but interpreted with greater caution due to their supplementary nature.

When a statistically significant effect is observed, the post hoc test will be performed using the Bonferroni correction to adjust for multiple comparisons. This correction will be applied systematically to all post hoc analyses to address the multiplicity of secondary outcomes.

For qualitative variables, the Chi-square test or Fisher’s Exact statistic will be used. The effect size will be calculated using Cohen’s d. Cohen’s coefficients [53] are interpreted as follows: large effect sizes, d > 0.8; moderate effect sizes, d = 0.5–0.79; and small, d = 0.2–0.49. The significance level was established at *p* < 0.05 with a 95% confidence interval. Missing data will be handled using Little’s MCAR test and multiple imputation (MICE) performed separately for each intervention group using the SPSS multiple imputation module. The analysis will be undertaken on an “intent-to-treat” basis.

Adherence outcomes (percentage of sessions completed, weekly frequency, and session duration) will be analyzed descriptively and compared between groups. If appropriate, exploratory analyses (e.g., correlation or regression models) will be conducted to examine the potential mediating or moderating role of adherence in relation to functional outcomes.

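### The post hoc Bonferroni correction is said to handle multiplicity across the secondary outcomes, but it acts only within one outcome and leaves every omnibus test at 0.05

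*Protocol article*

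**What the plan says.** Section 2.5 acknowledges that there are many secondary outcomes, asks for cautious interpretation, and promises that "multiplicity will be addressed using appropriate statistical adjustments, as detailed in Section 2.8".

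Section 2.8 sets out the procedure:

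- **Model:** "a mixed 3 × 3 ANOVA will be carried out with interaction time (three measurement time points) and group (three intervention groups").
- **Threshold:** "The significance level was established at *p* < 0.05 with a 95% confidence interval". No other level is given for any outcome.
- **Where the model applies:** the primary outcome and the 5 "Key Secondary Outcomes (motor function, muscle tone, muscle strength, balance, and quality of life) will be analyzed following this main model". The "Additional Secondary Outcomes (gait performance, perceived pain, fatigue, fall risk, and subjective perceived change) will be analyzed using the same statistical approach", but are to be read with greater caution.
- **Adjustment:** "When a statistically significant effect is observed, the post hoc test will be performed using the Bonferroni correction to adjust for multiple comparisons".
- **Purpose claimed for it:** "This correction will be applied systematically to all post hoc analyses to address the multiplicity of secondary outcomes".

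The article gives no split of alpha over outcomes, no testing order and no false discovery rate. The Key/Additional division affects only how cautiously results are read.

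**The concern.** Two kinds of multiplicity are treated as one. The first is the set of pairwise comparisons inside a single outcome, where a post hoc Bonferroni correction belongs. The second is the number of outcomes, each with its own ANOVA tested at 0.05. Section 2.8 applies a remedy for the first and says that it deals with the second. This is a positive statement about what the procedure achieves, so it is not a detail that can be left to a separate analysis plan.

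The stakes are real but limited. Quality of life is part of the study objective, yet it is a Key Secondary outcome. The Conclusions link possible adoption in primary care to several variables that include muscle strength, balance and perceived quality of life, all of them Key Secondary. A reader who trusts Sections 2.5 and 2.8 would take a significant result on one of these as protected against the number of outcomes tested.

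**Working it through.** **The plan's own figure.** The article states no family-wise error rate. Its only computed figure is the sample size of 75 (Section 2.3). It can be reproduced as a between-groups test in a repeated-measures design with f = 0.32, three groups, m = 3 time points, α = 0.05 and power 0.80, assuming a correlation of 0.5 between time points (not stated in the article). Then λ = f²·N·m / (1 + (m − 1)ρ) = 0.1024 × 66 × 3 / 2 = 10.1, which gives power 0.801 at N = 66. Allowing for 10% dropout, 66 / 0.9 = 73.3, so 74, or 75 for three equal groups. The full 0.05 goes to one outcome, the Barthel Index, and the secondary outcomes play no part in the calculation.

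**Number of secondary outcomes.** There are 5 Key outcomes. Table 1 lists 6 Additional instruments that fall under the ANOVA: the Wisconsin Gait Scale, 4-metre gait speed, Brief Pain Inventory, Fatigue Severity Scale, Timed Up and Go and Global Rating of Change. Adherence is analysed separately. That makes 11. The Global Rating of Change records perceived change after treatment and has no natural T0 value, so 10 is also defensible.

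**What Bonferroni does here.** The divisor is not printed. With three pairwise group contrasts, each would be tested at 0.05 / 3 = 0.0167 within that outcome. The omnibus test that opens the step stays at 0.05, whatever divisor is used afterwards.

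**Omnibus tests.** With one test per outcome, no true effects and independent outcomes, the chance of at least one false positive is 1 − 0.95^k:

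- k = 5: 1 − 0.95^5 = 0.226
- k = 10: 1 − 0.95^10 = 0.401
- k = 11: 1 − 0.95^11 = 0.431

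A simulation of the group × time test (25 per group, 2000 runs) agrees, with 0.22 for 5 outcomes and 0.42 for 11. At an assumed inter-outcome correlation of 0.5 it gives 0.18 and 0.33. A simpler simulation with equally correlated normal test statistics gives 0.18 and 0.30.

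**Pairwise findings.** The same 2000-run simulation, with no true effects, compared the three group pairs at T1 and again at T2, with Bonferroni × 3 at each time point (an assumed divisor). The chance of at least one false pairwise finding was as follows, with ranges covering correlation 0 and 0.5:

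| Outcomes | Interaction must be significant | Any effect opens the step, so it no longer filters |
|---|---|---|
| 1 | about 1% | about 7% |
| 5 (Key) | about 5% | 28–32% |
| 11 | 11–13% | 46–61% |

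Simulation error is at most √(0.5 × 0.5 / 2000) = 1.1 percentage points (one standard error). The right-hand column matters because Section 2.8 does not say which significant effect is needed. A time effect shared by all three groups would open the step without any difference between groups. Part of that column comes from correcting each time point separately, but a divisor that held each outcome at exactly 5% would still give 1 − 0.95^5 = 23% over 5 independent outcomes.

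In every variant the error rate grows with the number of outcomes, so the step does not control it across outcomes.

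**The case against.** The strongest reply is that little depends on this. There is a single primary outcome, the cross-outcome problem does not touch it, and the sample size was set on it alone. The secondary outcomes are tiered, and both Section 2.5 and Section 2.8 ask for caution. Leaving secondary outcomes unadjusted is common and would not be a fault if stated plainly. All of this stands and lowers the severity. It does not rescue the sentence, because caution in interpretation is not error control and the plan claims more than caution.

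A second reply is that the divisor is unstated and a full analysis plan might widen it across outcomes. That is possible, but the omnibus tests would still each be at 0.05.

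Three stronger readings are tempting and are not supported:

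- **That every secondary claim carries an error rate several times 5%.** This is true of omnibus tests and of pairwise findings under a loose gate. If only the interaction opens the post hoc step, false pairwise findings for the 5 Key outcomes stay near 5%. That result holds under the complete null and is a by-product of the gate, not a cross-outcome correction.
- **That having three F tests in each ANOVA adds to this problem.** With three independent tests, 1 − 0.95^3 = 14% for a single outcome. That is multiplicity within one outcome, and it counts the time main effect, which is not a treatment claim.
- **That the trial's main conclusion is compromised.** Nothing here affects the Barthel analysis.

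**Conclusion.** The statement is wrong as written: the procedure lacks the property that Section 2.8 claims and Section 2.5 relies on. Severity is moderate.

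The omnibus figures to carry forward are about 23% for the 5 Key Secondary outcomes and 40–43% for all 10–11, under no true effects and independence. At an assumed correlation of 0.5 they are about 18% for 5 outcomes and 30–33% for 11. The pairwise rate for the Key outcomes cannot be fixed from the text. It lies near 5% or at 28–32%, depending on which effect opens the post hoc step and on the assumed divisor of 3 at each time point. The outcome count takes one score per instrument; analysing subscales or separate limbs would raise it.

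**What to change.** **Minimum.** Delete the claim in Section 2.8 that post hoc Bonferroni deals with multiplicity across secondary outcomes, amend the pointer in Section 2.5, and label secondary results as not multiplicity-controlled. This cures the misstatement.

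**Preferred, because it keeps what Section 2.5 promises.**

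- Name one p-value for each Key Secondary outcome: the group × time interaction or a pre-named between-group contrast. The group main effect is a poor choice, since it averages in T0, where randomised groups are not expected to differ, and so dilutes a treatment effect.
- Apply Holm at 0.05 across the 5 Key outcomes, so that the smallest p-value is compared with 0.05 / 5 = 0.010. Testing them only after a significant primary result is a valid option but not a necessary one.
- Report the Additional outcomes as estimates with 95% confidence intervals.
- Keep Bonferroni for pairs within an outcome, and state which effect opens that step.

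**Cost.** The sample size and data collection do not change. Some secondary p-values become less favourable. The preferred version changes a decision rule in a registered, ethics-approved trial that is already recruiting, so it must be documented as an amendment before unblinded analysis.

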## 2. Materials and Methods

### 2.1. Study Design and Setting

This study is an assessor-blinded, multicenter trial with a ten-week treatment period followed by a two-month follow-up. It follows the consensus-based core recommendations from the stroke recovery and rehabilitation expert group [18], thereby improving the study’s development and the SPIRIT statement [30]. This study has been approved by the Research Ethics Committee of the Institut d’Investigació en Atenció Primària Jordi Gol (IDIAP Jordi Gol) (num. 24/190-P). It has been registered at ClinicalTrials.gov (NCT06944197). Participants will be randomly allocated in a 1:1:1 ratio to the control group (CG) (*n* = 25) or the experimental groups (EG1) (*n* = 25); (EG2) (*n* = 25). Patients are being recruited by five primary care centers of the Southern Metropolitan Management of the Institut Català de la Salut (ICS) in Catalonia, Spain.

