### 2.5. Outcome Measure

Descriptive data of the sample will be recorded, as well as anthropometric data and various assessment measures for the following evaluation variables.

The primary outcome is the degree of dependence or functional capacity for activities of daily living, which is assessed using the Barthel Index [32], and it is the validated scale used for the sample calculation [31].

The secondary outcomes have been classified into two categories: (1) Key Secondary Outcomes, which include motor function, muscle tone, muscle strength, balance, and quality of life, and (2) Additional Secondary Outcomes, which include gait performance (gait pattern and gait speed), perceived pain, fatigue, fall risk, subjectively perceived change after treatment, and adherence to the exercise program.

The secondary variables and their respective evaluation tools are as follows: motor function will be assessed using the Modified Motor Assessment Scale; muscle tone of the affected limbs will be measured with the Modified Ashworth Scale; muscle strength of the affected limbs will be evaluated using the Medical Research Council scale; balance will be assessed with the Postural Assessment Scale for Stroke Patients; walking efficiency will be measured using the Wisconsin Gait Scale and the 4 Meter Gait Speed Test; perception of osteomuscular pain will be evaluated through the Brief Pain Inventory; perception of fatigue will be measured using the Fatigue Severity Scale; fall risk will be assessed with the Time Up and Go Test; quality of life perception will be evaluated using the Newcastle Stroke-Specific Quality of Life Measure (Spanish version); and perception of subjective change post-treatment will be measured with the Global Rating of Change Scale (Table 1).

Adherence, included as an Additional Secondary Outcome, will be quantified as the proportion of prescribed sessions completed, the weekly frequency achieved, and the duration of each session, allowing further analysis of its potential influence on the functional outcomes observed across the intervention groups.

Although this broad set of outcomes aims to provide a comprehensive clinical profile of participants, the assessment burden is minimized through efficient scheduling of evaluation visits, grouping compatible measures within the same session, and using validated instruments with short administration times.

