The Fatigue Severity Scale (FSS) evaluates the severity of fatigue and its impact on daily activities, with scores ranging from 1 (strongly disagree) to 7 (strongly agree). The FSS is highly reliable for monitoring fatigue in stroke rehabilitation [44].

The Timed Up and Go (TUG) Test assesses fall risk by timing how long it takes for a patient to stand up from a chair, walk 3 m, turn, return, and sit down. The TUG test is a reliable and valid measure for fall risk [45].

The Newcastle Stroke-Specific Quality of Life Measure (NEWSQOL) evaluates stroke-specific quality of life, encompassing physical, emotional, social, and cognitive domains. It has demonstrated high internal reliability and strong construct, concurrent, and predictive validity [46].

The Global Rating of Change Scale (GROC) measures the patient’s perception of changes in their health or functioning after an intervention. It demonstrates strong test–retest reliability and robust concurrent and construct validity [47].

Information regarding stroke diagnosis, medical history, and stroke onset will be collected from patient records in the ECAP programs (ICS). Additionally, data on participant characteristics, including sex, age, family support, primary caregiver involvement, medication use, comorbidities, dysphagia, lesion location and side, time post-stroke, and stroke severity (assessed by the NIHSS and modified Rankin Scale), will be gathered for comprehensive analysis.

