### 2.6. Interventions

#### Intervention Description

The sample will be randomized systematically and pseudonymized. The 75 subjects will be divided into three intervention groups, and a different intervention will be carried out in each of them:

-Guidance Document Group (*n* = 25): The primary and community care physiotherapist will carry out an individual face-to-face consultation at the Primary Care Center with the person participating in the study, where they will deliver a guide document for the management of the pathology, as well as guidelines for the promotion and prevention of important health issues after a stroke. The document is the “Guide aimed at people affected by cerebral vascular disease and their families and caregivers” created by the Department of Health of the Generalitat de Catalunya, together with the Stroke Foundation in 2022. This group is the control, since the intervention is the one that most resembles the intervention that is currently being carried out in Catalonia from the Primary Care Centers for Stroke in the chronic phase.

No additional therapeutic contacts are scheduled after this initial session, and no monitoring is performed, as this reflects current standard practice in Catalonia.

No adherence tracking applies in this group, as no structured exercise program is prescribed.

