To ensure consistency across intervention groups, participants will be instructed to maintain only their usual daily physical activity during the study period. No additional structured physiotherapy, private rehabilitation, or external therapeutic exercise programs will be permitted, as these could influence the outcomes of the assigned intervention. Compliance with these instructions will be monitored through a weekly activity log completed by participants and reviewed by the physiotherapists, allowing the identification of any concomitant activities.

In addition, with the aim of analyzing the actual dose of treatment received, adherence will be assessed in all intervention groups based on the proportion of prescribed sessions completed, the weekly frequency achieved, and the duration of each session. These parameters will be systematically recorded to determine the effective exercise dose performed by each participant and to explore its potential influence on functional outcomes.

Finally, once the intervention period and the two-month follow-up evaluation (T2) have been completed, if the Telerehabilitation Group demonstrates superior results compared with the other two groups, participants from those groups will be offered the opportunity to receive an individualized therapeutic exercise program through the Physitrack platform. This measure ensures that all participants may benefit from the most effective therapeutic option, thereby upholding the ethical principles of equity and beneficence in research.

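### An unadjusted correlation of adherence with function cannot show mediation or moderation and can produce a false dose link; adherence is also undefined in the control arm

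*Protocol article*

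**What the plan says.** Section 2.8 of the protocol article first has adherence described and compared between groups. It then adds, conditionally, that "exploratory analyses (e.g., correlation or regression models) will be conducted to examine the potential mediating or moderating role of adherence in relation to functional outcomes". It states no covariates and no choice of arms for that step.

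Two other sections say what the analysis is for. Section 2.6 records adherence "to determine the effective exercise dose performed by each participant and to explore its potential influence on functional outcomes". Section 2.5 classes it as an Additional Secondary Outcome, measured by sessions completed, weekly frequency and session duration, "allowing further analysis of its potential influence on the functional outcomes observed across the intervention groups".

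Section 2.6 makes two statements about the control arm that do not agree. Under the control group's description: "No adherence tracking applies in this group, as no structured exercise program is prescribed". Later in the same section: "adherence will be assessed in all intervention groups based on the proportion of prescribed sessions completed".

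Section 2.5 (Assessments) lists baseline descriptors, including "lesion location and side, time post-stroke, and stroke severity (assessed by the NIHSS and modified Rankin Scale), will be gathered for comprehensive analysis". They are not tied to the adherence analysis.

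**The concern.** The question and the named tools do not match. Mediation asks whether allocation changes adherence and adherence in turn changes function. Moderation asks whether the treatment effect differs by level of adherence. A correlation between adherence and function addresses neither. Its null hypothesis is that the two are unrelated, and that is false whenever a third variable drives both, even if completing sessions does nothing.

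Baseline function is an obvious candidate for that third variable: a more able patient may find sessions easier to complete and will tend to score higher at T1. Section 2.6 also ties progression to good technique without excessive fatigue or pain, so the load delivered follows the patient's condition. Because sections 2.5 and 2.6 speak of dose and its influence on function, a significant correlation could be read as evidence that more sessions help.

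The control arm raises a separate problem. With no sessions prescribed, the proportion of prescribed sessions completed has no value there.

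**Working it through.** **Plan's own figure.** There is none for this analysis, so nothing can be reproduced.

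**Inputs from the article.** 25 participants per arm (sections 2.1 and 2.3) and two arms with prescribed sessions give 2 × 25 = 50. The 10% dropout of section 2.3 leaves 50 × 0.9 = 45.

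**Assumptions (not in the documents).** No effect of adherence on function. Baseline-adherence correlation *a* = 0.2, 0.3 or 0.4. Baseline-T1 correlation *b* = 0.6 or 0.8. Baseline function is the only shared cause.

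**Step 1: spurious correlation.** With no dose effect, corr(adherence, T1) = *a* × *b*.

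**Step 2: chance of p < 0.05.** By Fisher's transformation, z = atanh(*ab*) × √(n − 3), and the rejection rate is Φ(z − 1.96) + Φ(−z − 1.96). For n = 50, √47 = 6.856. Example: *a* = 0.4 and *b* = 0.8 give *ab* = 0.32, atanh = 0.332, z = 2.27, rate = 62%.

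**Step 3: simulation of the same setting** (n = 50, two-sided 0.05):

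| *b* | *a* | *ab* | Fisher | Simulated, unadjusted | Simulated, T0 value in model |
|---|---|---|---|---|---|
| 0.6 | 0.2 | 0.12 | 13% | 13% | 5% |
| 0.6 | 0.3 | 0.18 | 24% | 24% | 5% |
| 0.6 | 0.4 | 0.24 | 39% | 39% | 5% |
| 0.8 | 0.2 | 0.16 | 20% | 20% | 5% |
| 0.8 | 0.3 | 0.24 | 39% | 40% | 5% |
| 0.8 | 0.4 | 0.32 | 62% | 63% | 5% |

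At n = 45 the unadjusted range is 12% to 58%. With *a* = 0, the unadjusted test holds about 5% at either *b*.

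**Step 4: change scores.** If T1 − T0 is used instead, the spurious correlation is −*a* × √((1 − *b*)/2). At *b* = 0.8 that is −0.06, −0.09 and −0.13 for the three values of *a*, with rejection in 7%, 10% and 14% of trials. The sign is reversed: sessions would appear to do harm.

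**Step 5: control arm, from the text.** The measure is the proportion of prescribed sessions completed. Controls have none prescribed and are not tracked, so the denominator is zero and the measure is undefined. Mediation of exercise versus control through this measure cannot be estimated, and the measure cannot moderate that contrast. Only telerehabilitation (EG2) versus paper exercises (EG1) remains. Even there, the Introduction asks whether the format changes adherence, so adherence may be a consequence of allocation and is not a baseline effect modifier.

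**The case against.** The strongest reply is that section 2.8 commits to very little. The step is conditional, labelled exploratory, and introduced by an open list of examples. Regression is a normal way to fit both mediation and moderation, so the wording allows a properly adjusted model. Covariates for such a step are usually left to an analysis plan, which is not shown here. This stands as far as it goes: the absence of a covariate list is not the finding. It does not rescue correlation, which the article names as a tool for a question it cannot answer, nor does it settle the control-arm contradiction.

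A reader might infer four stronger things that the documents do not support:

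- **That the trial will report a false dose effect.** This needs baseline function to drive adherence and the T1 analysis to be unadjusted. Neither is stated, and the change-score version errs in the opposite direction.
- **That a stated aim of the trial fails.** The adherence aim in the Introduction is the comparison of telerehabilitation with paper delivery. The between-group comparison in section 2.8 covers it.
- **That controls will be entered as zero adherence.** Nothing says so.
- **That entry runs from Barthel 60 to 100, ensuring a wide spread.** The exclusion in section 2.4 refers to previous capacity and can be read as status before the stroke.

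It is also fair to say that adjustment returns to 5% by construction, since baseline function is the only confounder simulated. Unmeasured causes such as motivation would remain, which is why the result should be reported as an association.

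**Conclusion.** The point holds in limited form. Correlation is offered for a mediation or moderation question that it cannot answer. If better baseline function goes with more sessions, the unadjusted T1 version gives a false dose link in about 13% to 63% of trials at n = 50, against about 5% with the T0 value included. Those figures rest on assumed correlations and a true dose effect of zero.

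The control-arm point rests on no assumption. Section 2.6 contradicts itself on whether controls have adherence data, and the defined measure has no meaning for them. Severity is low: the analysis is exploratory, and no primary or key secondary conclusion depends on it.

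**What to change.** In section 2.8, replace the exploratory sentence with wording such as:

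> *In the two exercise arms only, the T1 outcome will be regressed on the proportion of sessions completed, adjusted for the T0 value of that outcome and for arm. Estimates will be given with 95% confidence intervals and described as associations, not as a causal effect of dose.*

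Baseline modified Rankin score may be added as a covariate. Drop the reference to moderation. If mediation is kept, limit it to EG2 versus EG1, use the same adjustment, and state the assumption of no unmeasured confounding between adherence and outcome.

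In section 2.6, reconcile the two statements on control-arm adherence, and align the phrase about the intervention groups in section 2.5 with the result.

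Cost: a wording change using data already collected. The downside is a weaker exploratory claim and one or two degrees of freedom.
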